### Setting

Regarding the setting, at baseline (T1), individuals consenting to participate in the study were randomly assigned it to two groups in the order that received an answer to the intervention or control groups by the online research service company. The researchers were not involved in this allocation in any way. All participants received a notification e-mail informing them of their allocated groups. The groups were listed as P Group (intervention group) and Q Group (control group) to prevent participants from knowing which group they were assigned to. This study is signal a type of single blinding. Because it is not the intervention of face to face, there is no contact during the intervention period.

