## Methods

### Study design

This study describes a two-armed, matched-design, web-based RCT. The nutrition education programme that we have developed as part of a health promotion project (Fig. 1). The intervention period is 5 weeks. The RCT is designed in line with the CONSORT statement for randomised trials of non-pharmacologic treatment [28]. Participants were assessed at three points in time: at baseline (T1), at post intervention (5 weeks later; T2), and at a follow-up at 3 months (T3). The participants were randomly assigned to one of two conditions: the intervention group and the waiting list group (i.e., the control group).

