Study participants were recruited using the following procedure. Of the approximately 160,300 registered monitors (as of September 2015), participants randomly to match the sex, age [30], and household income [29] distributions of Japan. Only study participants received an e-mail containing the website URL and password. Participate in the study were randomly assigned it to two groups in the order that received an answer to the intervention or control groups by the online research service company. The web-based nutrition educational programme is available in HTML format. Respondents who completed the questionnaire and clicked the ‘send’ button at the end of the online informed consent form were considered to have consented to survey participation (*n* = 1500). The research service company offered reward points valued at 40 JPY (in October 2015, one USD was equivalent to approximately 121 JPY) at T1. Of these, individuals who were allocated to the intervention group were offered reward points valued at 300 JPY after completion of the intervention (T2). Respondents from the control group were offered reward points valued at 40 JPY at T2. The participants were again offered reward points valued at 40 JPY for completing the assessment at 3 months after the completion intervention (T3; i.e. 4 months after the completion of the baseline survey [T1]).

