### Strengths and limitations

This study has three main strengths. First, this is an RCT using high-quality research methods. Because the RCT participants were assigned randomly, there is very little allocation bias. Additionally, randomization took place after acquiring consent to participate, which means that the intervention group was not populated only with participants actively interested in the research topic. This helps in avoiding over-estimation of the effects of the nutrition education programme in the intervention group. Second, this is nutrition education programme was web-based, thus making it highly accessible. Furthermore, the study was carried out by a social research company with a wealth of experience in implementing academic research surveys. These points ensured high feasibility while minimizing the burden of securing an adequate sample size to increase statistical power. In addition, participants could be extracted to match the distribution of sex and age in the Basic Resident Register and household income in the Comprehensive Survey of Living Conditions. For this reason, possible confounding effects could for the most part be eliminated at the stage of allocation. Third, the programme affords numerous advantages for both participants and supporters. Participants can take part when they are free to do so (e.g. time, place, and scheduling). As this means that they can take part even if they are located far away from the researchers, it would be highly convenient for participants [26]. The programme also offers supporters the opportunity to provide a unified nutrition education programme that is not reliant on the number of participants and to provide support without being subject to spatial or geographical restrictions. While it is true that the initial cost is somewhat considerable, its operational costs are low. The economic burden on supporters is thus small. Furthermore, passwords can be set for browsing the nutrition education programme, which can prevent communication between groups that could impact the quality of research.

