The RCT in this study is original in the following two regards. (1) It can verify the intervention effect for an adequate sample size, and (2) it can verify differences in the effect of a nutrition education programme by income strata. With this study, it will also be possible to verify the possible catch-up effect in relation to undesirable vegetable intake behaviour associated with low household income. Some reports have suggested that traditional classroom-based nutrition interventions might widen this disparity [6]. In contrast, with our study, it may be possible to show that a web-based nutrition education programme would inhibit the widening of this disparity.

Conversely, this study also has its limitations. It is possible that the results of the study will reflect the characteristics of individuals registered with the research company (e.g., tending to be young, high-earning, and highly educated [51–53]). To minimize this potential limitation, we have made sure to match participants with demographic distributions in terms of sex, age, and household income. In addition, we requested research cooperation from individuals whose household income data – which was our objective – had been recorded in advance. This helps to restrict attribute bias as well as negative response rates for delicate questions pertaining to household income and other matters. Second, during participant recruitment, we excluded individuals reporting household incomes of ten million JPY or more. This means that the results do not target the entire population. Accordingly, care must be taken when drawing general conclusions. However, a limit of less than ten million JPY still applies to 88.4% of the Japanese population. Finally, participants did not have contact with one another (either in person or through indirect communication) for the period of the intervention. For this reason, it is possible that rates of adherence to nutrition education programmes will be lower than they would with enforced participation.

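### The allocation sentence leaves open whether reply order decided the arm, and matching the sample to the population is wrongly credited with removing confounding at allocation

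*Protocol article*

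**What the plan says.** The allocation mechanism is described in two places in the Protocol article, in nearly the same words. Under Setting: "individuals consenting to participate in the study were randomly assigned it to two groups in the order that received an answer". The account under Recruitment source and procedure reads: "randomly assigned it to two groups in the order that received an answer to the intervention or control groups by the online research service company". Setting adds that "The researchers were not involved in this allocation in any way".

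The Study design section opens with "This study describes a two-armed, matched-design, web-based RCT".

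Strengths and limitations makes two separate claims:

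- On allocation: "Because the RCT participants were assigned randomly, there is very little allocation bias".
- On confounding: it notes that "participants could be extracted to match the distribution of sex and age in the Basic Resident Register and household income", and concludes "For this reason, possible confounding effects could for the most part be eliminated at the stage of allocation".

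Later in the same section, matching to national distributions is given another purpose, namely to offset the unrepresentativeness of a commercial panel: "To minimize this potential limitation, we have made sure to match participants with demographic distributions in terms of sex, age, and household income".

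**The concern.** There are two distinct problems.

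**Allocation wording.** Random assignment and assignment by order of reply are different procedures, and the sentence joins them. If reply order only fixed each person's position in a random list, the trial is properly randomised. If reply order determined the arm, it is not. Were the arms filled first-come, arm would be confounded with promptness, which plausibly tracks engagement with a web programme. The first strength claimed for the trial rests on this unresolved sentence.

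**Confounding claim.** Making the sample resemble the population bears on generalisability. It says nothing about whether the two arms resemble each other; random allocation, with or without stratification, does that. The article therefore claims a property that its sampling step cannot give, and the matched-design label invites the same misreading.

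**Working it through.** The plan states no figure on this point to reproduce. The check compares the passages and then sizes the possible readings.

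**Inputs from Sample size.** 900 intervention and 600 control, with expected dropout of two-thirds and one-half. Expected completers are 900 × 1/3 = 300 and 600 × 1/2 = 300. The intervention share at allocation is 900/1500 = 60%.

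**Assumed input.** r, the correlation between promptness of reply and outcome. The document gives no value, so a range is shown.

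**Reading A: first 900 replies to intervention, last 600 to control.** Take promptness as standard normal, cut at 60/40.

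- Density at the cut: φ(0.2533) = 0.386.
- Difference in mean promptness between arms: 0.386/0.6 + 0.386/0.4 = 1.61 SD.
- Bias in the outcome: 1.61 × r SD.
- SE with 300 completers per arm: √(2/300) = 0.0816 SD. This assumes that dropout leaves the difference unchanged.
- SE with all 1500: √(1/900 + 1/600) = 0.0527 SD.
- Type I error: P(Z > 1.96 − bias/SE) + P(Z < −1.96 − bias/SE).

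At r = 0.10 the bias is 0.161 SD. With 300 per arm, 0.161/0.0816 = 1.97 and the type I error is about 50%. With all 1500, 0.161/0.0527 = 3.05 and it is about 86%, as a simulation of 2000 trials with no true effect also found.

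| r (assumed) | Bias (SD) | Type I error, 300 per arm (formula) | Type I error, all 1500 (simulation) |
|---|---|---|---|
| 0 | 0.00 | 5% | 5% |
| 0.05 | 0.08 | 17% | 31% |
| 0.10 | 0.16 | 50% | 86% |
| 0.20 | 0.32 | 98% | 100% |

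**Reading B: fixed 3:2 rotation by reply order.** In the same simulation, for r from 0 to 0.30, bias is about 0 and type I error is 3.6% to 4.7%. The sequence is predictable and not random, but it does not separate early from late repliers.

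**Reading C: a random sequence applied as replies arrive.** Bias is about 0 and type I error about 5%.

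Only Reading A produces material bias, and the text does not choose between the three.

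**Matching, set side by side.** Recruitment source and procedure, and both places in Strengths and limitations, describe matching the sample to national distributions. None describes pairing or matching participants between arms. Statistical analyses plans independent t-tests between groups, which fits unmatched arms. The inference from population matching to reduced confounding therefore fails under A, B and C alike.

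**The case against.** The strongest reply is that the article says random throughout: in the abstract, in Study design, in both allocation sentences and in Strengths and limitations, which adds that randomisation followed consent. In loosely worded English, the order-of-reply phrase can naturally mean one-by-one randomisation as replies came in. The company made the allocation and the researchers had no part in it. An article may also leave sequence generation to a fuller document.

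Much of this stands. A reader might infer that allocation was in fact non-random; the document does not support that, only that its wording does not exclude it. A reader might also take the 50% or 86% type I error as a finding about this trial. Those figures belong to first-come filling with an assumed r, and neither is stated anywhere. Separating the researchers from allocation limits their influence but does not make the company's sequence random.

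A further tempting reading is that not stratifying by income is an error. It is not. Simple randomisation is valid, and if half the sample were low-income (assumed), the SE of the between-arm difference in that share would be √(0.25 × (1/900 + 1/600)) = 2.6 percentage points. Stratifying at allocation would not secure balance among completers either.

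The reply does not rescue the confounding sentence. It sits in the Discussion, is hedged, and the analysis does not depend on it, but its reasoning is wrong under every reading.

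**Conclusion.** The point holds in two limited parts. First, the only description of the mechanism joins random assignment to order of reply and does not say which governed the arm. The resulting bias could be nil (a random list, or approximately so with a fixed rotation) or 1.61 × r SD (first-come filling, normal promptness score, r unknown). Until this is settled, the claim of very little allocation bias is unsupported rather than shown to be false. Second, crediting population matching with eliminating confounding at allocation is wrong whatever mechanism was used, and no described feature of the trial supports the matched-design label.

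**What to change.** 1. **If allocation is still to be done**, replace the sentence in both sections with wording such as: *Consenting respondents are allocated 3:2 to intervention or control by a computer-generated random sequence that does not depend on the order of reply.* Stratifying by household income, sex and age band is an optional gain; the company already holds these data.
2. **If allocation is complete**, as the past tense in Methods suggests (the abstract uses the future), state the mechanism actually used and do not write in a procedure that was not followed. If reply order decided the arm, withdraw the claim of very little allocation bias.
3. Delete the matched-design label in Study design and the confounding sentence in Strengths and limitations. Keep the population matching as a point about representativeness.
4. Adjust the between-arm analysis for sex, age and household income, all listed under Other measurements. This handles chance imbalance in those factors; it would not repair confounding by promptness.

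The cost is one query to the research company, a few changes of wording and three covariates in the model. No new data are needed.

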### Study sample

#### Recruitment source and procedure

A web-based intervention survey was conducted by a Japanese online research service company that contains data, including sociodemographic attributes, for approximately 160,300 adults aged 30–59 years. Participants were randomly selected based on Japanese population statistics for the present study. We targeted adults because of the necessity of health promotion, healthy eating, and reduction in health disparities for this age group [23]. The following inclusion criteria are considered: (1) men and women aged 30–59 years old; (2) able to understand Japanese; (3) can access the Internet at home, work, or a public place; (4) agree to access the study website during the 5-week intervention period; (5) will participate in all three assessment points during the 4-month study period. The exclusion criterion is having an household income of ten million yen or more (meaning that 88.4% of the total population is having an household income of ten million yen less) [29]. The study procedure from enrolment to follow up is depicted in Fig. 1.

The research company that we used in the present study periodically analyses and updates its registrant database. A notable characteristic of this company is that, to prevent bias among survey respondents, the firm requests the participation of the minimum number of respondents after taking response rate into consideration. Moreover, once every 6 months, the firm updates its monitoring information and conducts checks to safeguard against double registration or non-existent IP addresses. Registrants had been enrolled with the survey company by an open recruitment process.

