### Intervention group

Participants assigned to the intervention group received an e-mail containing the dates of programme updates, the website URL of the intervention programme, a password for browsing the website, and the following information.

The programme updates were sent on Monday morning of each week during the intervention period. Participants received a total of five e-mails on the nutrition education programme over the 5 weeks of the intervention period. On the first occasion, participants received an e-mail containing (1) instructions on how to access the website (i.e. the URL and password), (2) an overview of the programme and how it would proceed, and (3) the programme contents for the first week. The e-mails sent in the subsequent weeks, in addition to item (1–3), included (4) a review of the contents of the previous step. The programme website was made freely accessible only for the duration of the intervention period, and after which it was closed. Participants’ passwords were effective for the duration of the study. If a participant forgot his or her password, it could be retrieved by contacting a research officer. After completion of the 5-week intervention, participants received an e-mailed request to participate in the post-intervention survey (T2). Finally, participants received another e-mail request to participate in a follow-up survey 3 months after completing the intervention (T3).

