### Control group

The control group surveys took place over the same period as intervention group surveys. Control group participants received an advance notification e-mail after the baseline from the survey company that another survey would take place 5 weeks later. After a 5-week-long silence, participants received an e-mail request to take part in the post-intervention survey (T2). Subsequently, participants received an e-mail request to participate in a follow-up survey 3 months later (T3).

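### The P/Q labels do not blind participants: those given the programme know it, controls can probably infer their arm, and participants report the outcomes, so the single-blind statement is wrong as written

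*Protocol article*

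**What the plan says.** All places are in the protocol article.

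- **Setting.** Every participant is told a group label: "All participants received a notification e-mail informing them of their allocated groups". The labels are P (intervention) and Q (control), chosen "to prevent participants from knowing which group they were assigned to". The section then states: "This study is signal a type of single blinding". It adds that the researchers took no part in allocation.
- **Intervention group.** "Participants received a total of five e-mails on the nutrition education programme over the 5 weeks of the intervention period". The first e-mail carries the URL and password, an overview of the programme, and the first week's content.
- **Control group.** After baseline, controls get one advance notice that another survey will follow. Then: "After a 5-week-long silence, participants received an e-mail request to take part in the post-intervention survey (T2".
- **Study design.** The two conditions are "the intervention group and the waiting list group (i.e., the control group"). No sham or attention programme is described.
- **Recruitment source and procedure.** One inclusion criterion, for all entrants, is that they "agree to access the study website during the 5-week intervention period". Rewards at T2 are 300 JPY in the intervention arm and 40 JPY in the control arm.
- **Assessment, Primary outcomes, Secondary outcomes.** Subjective diet-related quality of life, self-rated health, the eating behaviours, daily vegetable servings and daily grams of vegetables are all answered by the participant.

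**The concern.** The article names participants as the people kept from knowing their group, and a neutral letter as the means. A letter hides the arm only if what follows is similar in both arms. Here one arm gets a five-week vegetable programme and the other gets none.

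Participants also report every primary and eating-behaviour outcome, so the unblinded person is the outcome assessor. Only the intervention arm spends five weeks being taught the serving target and is then asked how many servings it eats. Over-reporting in that arm alone would look like a programme effect. A reader who accepts the single-blind label would give the self-reported differences more credit than the design earns, and the limitations in Strengths and limitations do not mention reporting bias.

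**Working it through.** The blinding statement contains no figure to reproduce. The check compares it with what each arm experiences.

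**1. Who is said to be blinded.** Setting names the participants. Reading the phrase as researcher blinding does not rescue it. The statements about researchers cover non-involvement in allocation (Setting) and receipt of anonymised data (Ethics approval). Neither says that arm was masked.

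**2. Can the intervention arm be blind?** No. Its members receive five programme e-mails, a password-protected site and an explanation of how the programme proceeds. They know they are receiving it, whatever letter they were given.

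**3. Can the control arm be blind?** Probably not. On the stated inclusion criteria they agreed to access a study website for five weeks; they then receive only an advance notice of a survey and five weeks of silence, on what Study design calls a waiting list. This is a strong inference and not a demonstrated fact, because the consent text is not shown and Control group mentions only notice of another survey.

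**4. Who assesses outcome?** The participant, for the primary outcomes and the eating behaviours. Log-ins and time on the site (Process evaluation) are not self-reported, but they are adherence measures.

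**5. Where is differential reporting most plausible?** For vegetable servings. Step 1 of Table 1 teaches that 350 g is five servings and has participants log their daily dishes. The action goal (Intervention programme) is five servings, or one more than before. The questionnaire (Secondary outcomes) then asks for servings per day. For quality of life and self-rated health, the route is only the general one of knowing that one received a programme.

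**6. Scale, for illustration only.** The document gives no bias figure, so a range is assumed. Expected completers from Sample size:
- intervention: 900 × (1 − 2/3) = 300
- control: 600 × (1 − 1/2) = 300

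For a standardised outcome, SE = √(2/300) = 0.0816. With no true effect and a reporting difference of b SD, the chance that a two-sided 5% test rejects is Φ(b/SE − 1.96) + Φ(−b/SE − 1.96).

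| Assumed b (SD) | False rejection |
|---|---|
| 0 | 5.0% |
| 0.05 | 9.4% |
| 0.10 | 23.2% |
| 0.20 | 68.8% |
| 0.30 | 95.7% |

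In servings, an assumed over-report of 0.2 serving in one arm is 0.2 × 70 g = 14 g, which is 14/70 = 20% of the trial's own target of about 70 g.

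**The case against.** The strongest reply is that participants usually cannot be blinded in a web education trial with a waiting-list control, that self-report is openly disclosed, and that blinding is not among the strengths the article lists. No sample size, test or estimate changes. All of this is true. It makes the point one of wording and interpretation, but it does not make the sentence in Setting correct.

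A reader might infer several stronger things that the document does not support:

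- **That both arms certainly know their allocation.** This is certain only for the intervention arm.
- **That the rewards give the arms away.** Strengths and limitations says participants had no contact with one another, and nothing shows that either arm saw the other's reward. The 300 versus 40 JPY difference is weak evidence.
- **That the article claims protection from reporting bias.** It claims only a type of single blinding.
- **That the absence of analyst masking is an error.** The article claims none, and a condensed protocol commonly leaves it to the full protocol or the statistical analysis plan.
- **That the existing P/Q codes could blind the analyst.** Setting prints what P and Q mean.
- **That a modest bias would equal half of a realistic effect.** An over-report of 0.2 serving is half of the 0.6 − 0.2 = 0.4 serving difference cited in Background. That comparison was against an information bulletin board and not a waiting list, and the bias is assumed.

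The coaching argument applies to vegetable intake, which the Abstract calls the main outcome but Methods lists as secondary. It is weaker for the primary outcomes named in Methods. The self-report problem applies to both.

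**Conclusion.** Wrong as written. The design does not have the participant blinding that Setting states. Intervention participants necessarily know they are receiving the programme, and controls can probably infer that they are not. Since participants report the primary and eating-behaviour outcomes, outcome assessment is not reliably blinded, and differential reporting could favour the programme, especially for vegetable servings.

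The size of any such bias cannot be estimated from the document. The false-rejection table rests on assumed biases, 300 completers per arm and a normal approximation; it shows only that small differences in reporting would matter at this sample size. The conclusion about the control arm assumes that the consent material did not hide the existence of a programme from people who had agreed to use a study website. The trial remains feasible and its planned tests are unaffected; what changes is what its results can be said to show.

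**What to change.** - In Setting, delete the single-blind statement and say plainly that participants, who report the outcomes, are not blinded. The P/Q labels may stay as administrative labels.
- In Strengths and limitations, add differential reporting bias, and note that only the intervention arm is coached on the serving target.
- Word conclusions as effects on self-reported outcomes, including self-reported vegetable intake.
- Optional: mask the analyst. This would need fresh arm codes held by the research company, because the meaning of P and Q is already disclosed. Masking would be only partial, since the 900/600 arm sizes and the process data collected only on the programme would tend to reveal the arms.

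The required changes are text only and cost almost nothing. The downside is a weaker stated design feature.
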